## Methods/design

### Study design

The study employs a clustered randomised controlled trial design. Ninety ECEC centres in NSW, Australia, will be recruited to ensure representation across National Quality Standards (NQS) ratings (Working Towards, Meeting, Exceeding), location (metro, regional), centre type (long-day care and preschool) and socioeconomic areas (as based on the Socio-Economic Indexes for Australia; SEIFA). The sample will ensure representation across these variables, but is not intended to be fully representative of the population (see ‘Centre characteristics and recruitment’ section below). Stratified random assignment of centres to control and intervention groups will occur after the collection of baseline environmental ratings. Once collected, participating centres will then be stratified by centre type and NQS rating and randomly allocated to one of two groups: (1) the *intervention* group (*n* = 45 centres) receiving the PD intervention or (2) the *control* group (*n* = 45 centres) that will continue engaging in typical classroom practice. Fieldworkers, blinded to group allocation, will then conduct baseline child assessments early in the following year. The 9-month PD intervention will occur throughout much of 2016. Post-intervention child assessments and environmental quality ratings will occur again in late-2016 to evaluate any changes as a result of the intervention, relative to control. A flowchart depicting the sequence of recruitment, intervention and assessment for FEEL is shown in Fig. 1. An outline of Standard Protocol Items: Recommendations for Interventional Trials (SPIRIT) time points and actions for the FEEL study is shown in Table 1 (see Additional file 1 for the trial’s SPIRIT Checklist).

**Fig. 1 Fig1:**
[figure not shown]
Flow diagram of the stages of the FEEL study

**Table 1 Tab1:** Standard Protocol Items: Recommendations for Intervention Trials (SPIRIT) table

	Study period				
	Enrolment	Allocation	Post allocation		
Time point	Pre intervention	Time (*t* _0_)	Centre baseline (*t* _1a_)	Child baseline (*t* _1b_)	Post intervention (*t* _2_)
Enrolment					
Eligibility screen	X				
Initial centre contact	X				
Centre informed consent	X				
Allocation		X			
Recruitment of children and parent informed consent		X			
Intervention					
PD intervention					X
Regular practice (control)					X
Assessments					
Child assessments					
DAS Verbal Comprehension				X	X
EYT Expressive Vocabulary				X	X
DAS Early Number Concepts				X	X
Early Numeracy Scales				X	X
Strengths & Difficulties (SDQ)				X	X
Child Self-Regulation (CSBQ)				X	X
Centre-level assessments					
ECERS-E Environmental Rating			X		X
SSTEW Environmental Rating			X		X

*PD* professional development, *DAS* Differential Ability Scales, *EYT* Early Years Toolbox, *SDQ* Strengths & Difficulties Questionnaire, *CSBQ* Child Self-Regulation and Behaviour Questionnaire, *ECERS-E* Early Childhood Environment Rating Scale – Extended, *SSTEW* Sustained Shared Thinking and Emotional Wellbeing scale

### Centre characteristics and recruitment

An initial list of ECEC centres in NSW, Australia (*N* = 348) will be examined for potential inclusion. Criteria for the potential inclusion of centres will be: (1) being within 1.5 h of one of the three study hubs, (2) being within socioeconomic (SEIFA) deciles 1–8 (thereby excluding very privileged areas), (3) not participating in other research and (4) not being a Department of Education (study funder) centre. A selection of 90 centres for initial approach will be made on the basis of representation across NQS ratings (i.e. approximately equal numbers of Working Towards, Meeting, Exceeding), service type (i.e. two thirds long-day care, one third preschool), location (i.e. approximately equal numbers of metro and regional centres) and socioeconomic areas (i.e. deciles 1–8, according to SEIFA Advantage and Disadvantage indices, with at least one third of the sample derived from areas of known deprivation). A backup list of centres will be created to supplement recruitment if initial approach is unsuccessful.

Centres will be invited to participate in the study first by an initial call to gauge interest and identify the best contact for follow-up. A member of the research team will then make a follow-up call to interested centres to more fully explain the study and, if appropriate, obtain a contact email address to send Participant Information Sheets and Consent Forms for review. Participating centres will be those that meet the inclusion criteria and return a signed Director Consent Form to participate in the study. The first 90 ECEC centres that respond positively to the invitation and give written consent will take part in the study.

### Randomised allocation of centres

The study will adopt a cluster randomised controlled trial design; participants (i.e. centres and children) will be assigned to the control or intervention groups randomly by cluster (centre). Randomisation will not occur until after: (1) recruitment of centres is complete and (2) initial baseline environment ratings are complete. As such, those involved in recruitment of centres will be unaware, at time of recruitment, to which group centres will be allocated. Stratified randomisation of centres (cluster) will be conducted using centre type and NQS rating as core stratification variables. This randomisation will also be evaluated to ensure comparable socioeconomic status (SES), environmental rating and location profiles between the two groups, which subsequent analyses will confirm.

### Child characteristics and recruitment

Early in the year following centre recruitment, and preceding the intervention, children in the year before formal schooling (4–5 years of age) will be recruited from participating centres. This involves disseminating Participant Information Sheets and Consent Forms, via the centre, to parents or legal guardians of suitably aged children. Participating children will be those who meet the age-inclusion criteria, returned a signed Parental Consent Form to participate in the study and themselves provide verbal assent to participate. Ninety centres are expected to yield a sample of approximately 1200 4–5-year-old children on whom child assessments will be conducted. There are no further exclusion criteria for child participation.

### Outcome measures and procedures

All measures will be administered at baseline and again after the 9-month intervention period (post-test). The battery of child measures was selected to include outcomes that are important for school readiness (i.e. literacy, numeracy, self-regulation, social development). Such outcomes have also been established by previous research as having a foundational role in child development. In total, the child outcome measurements involve 40–50 min of direct assessment per child (split into two sessions) and 10 min of educator time per child (i.e. approximately 3.3 h of educator time per centre) at each data collection time point. In all cases, child assessments will be carried out by a trained fieldworker in a quiet area of the child’s ECEC centre. All environmental quality ratings will also be conducted by highly trained observers through a 1-day observation of each preschool room in participating centres. All observers will need to achieve a rigorous standard of inter-rater reliability with a highly experienced trainer/observer, as indexed by: an intra-class correlation in ratings > .70; a mean difference in ratings < .75; and at least 80% of item ratings within 1 point. In all cases, the researchers involved in collecting baseline and outcome data will be blinded to each centre’s group allocation.

Primary child-level outcomes consist of measures of children’s language development: verbal comprehension and expressive vocabulary. Specifically, the Verbal Comprehension subtest of the Differential Ability Scales (retest reliability 0.82; concurrent validity 0.70) [32] is a measure of the receptive language (comprehension) ability of the child, and takes 10–15 min to administer. The Expressive Vocabulary test from the Early Years Toolbox (internal consistency 0.92; concurrent validity 0.60) [33] is an assessment of expressive vocabulary to complement the receptive language measure, and takes 5 min to administer. Secondary outcomes at the child level involve measures of early numeracy, social development and self-regulation. The Early Number Concepts subscale of the Differential Ability Scales (internal consistency 0.89; concurrent validity 0.71) [32] and the Early Numeracy Assessment [34] include numeric concepts of counting, cardinality, number comparison and number combinations (internal consistency 0.74 to 0.79; concurrent validity 0.35 to 0.66). These two assessments each take 10–15 min to complete. The educator-report Child Self-regulation and Behaviour Questionnaire (CSBQ) [33] and Strengths & Difficulties Questionnaire (SDQ) [35] yield subscales of cognitive, emotional and behavioural self-regulation, antisocial and prosocial behaviours, sociability and anxiety/internalising, among others. The CSBQ subscales have internal consistency ranging from 0.74 to 0.89, and concurrent validity in the range of 0.48 to 0.81 [33]. The SDQ subscales have internal consistency in the range of 0.65 to 0.85, and concurrent validity in the range 0.87 to 0.92 [36].

ECEC room-level secondary outcomes involve observational ratings of the quality of provision in centres using the Early Childhood Environment Rating Scale – Extended (ECERS-E) (inter-observer reliability 0.75 to 0.90 for subscales) [37] and the Sustained Shared Thinking and Emotional Wellbeing (SSTEW) scale (inter-observer reliability 0.79 to 0.92 for subscales) [38]. ECERS-E measures the quality of the curricula, environment and pedagogy in language and literacy, maths and number, science and environment, as well as quality related to meeting the needs of diverse students. The SSTEW scale is designed to consider practice that supports children aged 2 to 5 years in developing skills in SST and emotional wellbeing within five subscales: (1) building trust, confidence and independence, (2) social and emotional wellbeing, (3) supporting and extending language and communication, (4) supporting learning and critical thinking and (5) assessing learning and language.

### Professional development intervention

The PD programme is focussed on enhancing the quality of staff interactions and relational and intentional pedagogy with children. The programme, delivered in three distinct phases over 9 months, provides opportunities to observe, discuss, practice and reflect on important attributes of the effective educator’s role, including: engaging in high-quality interactions and SST, developing and extending concepts, and modelling critical and reflective thinking. Links are made to appropriate frameworks including the Australian NQS and the Australian EYLF. Fundamental to each session is evidence-based understandings of how young children learn best. The PD has been designed to support the collective participation of attendees, as well as to promote collaborative working to gain deeper knowledge of leadership, change management, quality improvement and self-assessment. The PD programme covers eight core content areas, delivered across three phases:Research on quality in ECEC and its assessmentHow high-quality interactions extend children’s developmentThe relevance of self-regulation to children’s educational successThe links between early language development and later literacyMathematical and scientific concept development in the early yearsWays to use observation, assessment of practice and planning to improve qualityThe importance of early home learning and connections across ECEC settings and the home learning environmentThe relevance of leadership for learning for children’s development and ways to improve it

#### Phase 1: Intensive professional development (week 1 to week 3, delivered at each of three hubs)

A 2-day, intensive, face-to-face training providing: an overview of national and international research; an introduction to relevant environmental quality characteristics; coverage of key concepts and ideas; as well as strategies to foster early language, cognitive, self-regulatory and social development, engagement in high-quality interactions, and work with homes.

#### Phase 2: Follow-up professional development (week 3 to month 3, delivered at each of three hubs)

Five 4-h, half-day, face-to-face sessions, delivered every 2 weeks, beginning 2 weeks after a hub’s completion of phase 1. The sessions include time for reflection, planning and critical analysis, as well as the introduction of knowledge and pedagogical content on areas not covered in phase 1.

#### Phase 3: Model for sustainability (week 3 to month 9)

To promote centre commitment, limit the effects of staff turnover and increase the likelihood of a positive impact, PD support will be provided for the full 9-month intervention through online modules (beginning at the end of phase 1 and continuing for 9 months). Activities and resources, designed to promote staff engagement and establish an online community of educators are contained within modules or *E-books*. Each E-book combines video-streamed content with questions and text, including links to activities and a discussion forum. Staff participation and discussions feed into a learning portfolio, tracking and reflecting how their ideas about pedagogy, children, families and communities have changed. Access to this online environment is provided to all centre staff, not only those attending phases 1 and 2.

#### Session details

All sessions will be delivered at each of three central hubs to ensure that all centres are within 1.5 h of the PD delivery location. Sessions are to be conducted by four of the study’s chief investigators, who are researchers and international experts in early childhood education and care. All sessions will be delivered in a group setting for centres most proximal to that hub.

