The effect of the PD intervention will be considered in two ways. Firstly, we will compare 45 intervention and 45 control centres for environmental quality in order to estimate the effect upon staff behaviour in the centres. ECEC room-level outcomes will be analysed using linear regression models with post-test outcomes as dependent variables and baseline measures as independent variables. Child-level data analyses will control for clustering within centres using multilevel models (hierarchical models or random-effect models), which can account for clustering of repeated assessments within individuals and clustering of individuals within centres. Post-test scores for primary and secondary outcomes will be used as dependent variables, with baselines variables and group membership as independent variables. Multiple imputation methods will be used for missing individual outcome data. If data are normally distributed we will fit linear models. If not, we will categorise outcome data and use longitudinal logistic regression to evaluate the differences between intervention and control groups. Sensitivity analyses will be conducted for all primary and secondary outcomes. Inverse probability weighting will be considered if missing data are more prevalent than expected and/or there is differential attrition between trial arms. Additionally, reasons for the differential attrition will be fully explored. Secondary analyses from explicit hypotheses (e.g. subgroup, including level of deprivation) will be specified in advance in a statistical analysis plan.

In applying power calculations, we took into account that children are clustered in centres.

Conservative power estimates, after adjusting for the clustered (nested) design, indicate that we can detect an effect size as low as 0.17 standard deviation (SD) units with 80% power for all child outcomes. This is based on a conservative estimate of 13 children per centre, yielding an estimated sample size of 1170. For continuous outcomes, these correspond to differences between the means in the treatment and control groups in units of the SD.

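### Face-to-face PD is delivered jointly in three hub groups, but no stated model contains hub: some precision may be lost, and the interval covers only these three deliveries (minor)

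*Protocol article*

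**What the plan says.** The Protocol article describes phases 1 and 2, which are all of the face-to-face PD, as given at each of three hubs. Phase 2 at a hub starts two weeks after that hub finishes phase 1, so the dates belong to the hub. Under Session details: "All sessions will be delivered in a group setting for centres most proximal to that hub". The deliverers form one pool ("Sessions are to be conducted by four of the study’s chief investigators"), and phase 3 is online: "PD support will be provided for the full 9-month intervention through online modules".

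Hub is defined for both arms. The first eligibility criterion under Centre characteristics and recruitment is "being within 1.5 h of one of the three study hubs".

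Hub does not appear in the allocation or the analysis:
- **Randomisation:** "Stratified randomisation of centres (cluster) will be conducted using centre type and NQS rating as core stratification variables".
- **Balance check:** "This randomisation will also be evaluated to ensure comparable socioeconomic status (SES), environmental rating and location profiles between the two groups". The Study design section describes location as metro or regional.
- **Child-level models:** "Child-level data analyses will control for clustering within centres using multilevel models". The levels named are repeated assessments within child and children within centre. The covariates named are baseline variables and group.
- **Room-level models:** linear regression of post-test on baseline.
- **Power:** allows for children clustered in centres.

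**The concern.** Intervention centres attached to the same hub share sessions, peers and dates. The 45 intervention centres therefore receive three group deliveries of the face-to-face PD, about 15 centres each if hubs are of equal size. The stated models treat them as 45 separate deliveries. Two things follow.

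1. **Precision.** If outcomes differ between hub catchments, leaving hub out puts that variation into the error term.
2. **Scope of the claim.** If one hub's delivery works better or worse than another's, all its intervention centres shift together. The article expects its results to inform practitioners and policy-makers about this kind of PD. For a claim about PD deliveries in general, delivery-to-delivery variation belongs in the uncertainty, and the plan neither includes it nor looks for it.

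**Working it through.** **Inputs from the Protocol article (Statistical analyses and power).** 45 centres per arm, 13 children per centre (585 children per arm), 80% power, detectable effects 0.17–0.20 (p < .05) and 0.21–0.24 (p < .01), or 0.16 and 0.20 if children were independent, and 0.60 at room level. Two-sided tests are assumed, as the article does not say.

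**Step 1: reproduce the stated power.** Detectable effect = (z for alpha + 0.842) × √(2 × DEFF / 585), with DEFF = 1 + 12 × ICC.
- Independent children: 2.802 × √(2/585) = 0.164 (stated 0.16); at p < .01, 0.200 (stated 0.20).
- Room level: 2.802 × √(2/45) = 0.591, or 0.597 with t quantiles (stated 0.60).
- Clustered: 0.17 and 0.20 correspond to DEFF 1.077 and 1.491, so ICC 0.006 and 0.041. 0.21 and 0.24 correspond to ICC 0.009 and 0.037.

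The two clustered ranges agree, and a modest centre ICC alone accounts for them.

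**Step 2: hub differences common to both arms.** Assume three hubs of 30 centres and centre ICC 0.04. The variance of a centre mean is 0.04 + 0.96/13 = 0.1138, so SE = √(2 × 0.1138 / 45) = 0.071. A hub SD of s adds (2/45) × s² × (2/3) × (90/89) to the variance when centres are allocated without regard to hub:
- s = 0.1: SE = √(0.00506 + 0.00030) = 0.073
- s = 0.2: SE = √(0.00506 + 0.00120) = 0.079

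In simulation (10,000 trials per setting, hub ignored in allocation and model), mean bias was 0.000 and type I error 0.049 (s = 0.1) and 0.051 (s = 0.2). At s = 0.2, a hub fixed effect brought the SE from 0.079 back to 0.072.

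For a single allocation, the number of intervention centres in a hub of 30 has SD √(45 × 1/3 × 2/3 × 45/89) = 2.2, so an 18 versus 12 split is not unusual. The arms' shares of that hub then differ by 18/45 − 12/45 = 0.133. If that hub differs from the other two by 0.10 SD, the contrast moves by 0.133 × 0.10 = 0.013 SD.

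**Step 3: PD effect varying between hub deliveries.** The detectable effects imply SE = 0.17/2.802 = 0.0607 to 0.20/2.802 = 0.0714. With three equal deliveries whose effects vary with SD s, the SE for the average effect over such deliveries is √(SE² + s²/3). The size of the nominal 5% test is 2 × [1 − Φ(1.96 × SE / SE for wider inference)].

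| Assumed delivery SD | SE for wider inference | Size of nominal 5% test |
|---|---|---|
| 0.03 | 0.063 to 0.073 | 0.059 to 0.057 |
| 0.05 | 0.067 to 0.077 | 0.077 to 0.069 |
| 0.10 | 0.084 to 0.092 | 0.156 to 0.128 |

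In each range the first value belongs to the 0.17 case and the second to the 0.20 case.

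**Step 4: does a hub fixed effect cure step 3?** No. At delivery SD 0.10 and centre ICC 0.04, simulated size was 0.122 without hub, and 0.127 with hub both as a stratum and as a fixed effect.

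**The case against.** A reader might infer that differences between hubs can be mistaken for a PD effect. The document does not support that. Every eligible centre, control or intervention, lies in a hub catchment, and centres are randomised individually, so hub differences are balanced in expectation. Chance imbalance is covered by the standard error. Step 2 shows no bias and no inflation, and the 0.013 SD shift compares with an SE of 0.061 to 0.071.

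A reader might also take the 6% to 16% as the false-positive rate of the planned test when the PD does nothing. It is not. If the PD has no effect at any hub, deliveries cannot differ in effect and the test keeps its size. The figures apply to a null of zero average effect over a wider set of deliveries, with some helping and some harming. The article itself says that its sample is not meant to be fully representative.

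The delivery SDs are assumptions, and an SD of 0.10 is at least half the detectable effect. One pool of deliverers, common core content and nine months of online support all argue for less divergence. This stands, and it keeps the point small.

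Finally, hub terms could be in a statistical analysis plan (SAP) that is not shown, and the article does promise sensitivity analyses. That is a fair limit. Still, the article does not merely stay silent on models: it fixes the clustering levels, the covariates and the basis for power, and what it expressly defers to the SAP is secondary analyses such as subgroups.

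**Conclusion.** The point holds as a minor one. Delivery in three hub groups is reflected in neither the stated models nor the power. The comparison of arms remains unbiased, and the planned test is valid for these three deliveries.

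The cost is some precision if hubs differ (SE about 0.073 to 0.079 against 0.071 at an assumed hub SD of 0.1 to 0.2), together with an interval too narrow for claims beyond these deliveries. The size of that second shortfall cannot be estimated from the document; the 6% to 16% range rests on assumed delivery SDs of 0.03 to 0.10. Both results also assume three equal hubs and two-sided tests, and the precision figures assume a centre ICC of 0.04.

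**What to change.** In Statistical analyses and power:

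1. Assign each of the 90 centres, control centres included, to its nearest hub, and enter hub (three levels) as a fixed effect in the child-level and room-level models. This recovers precision lost to hub differences.
2. As a supportive analysis, report the intervention effect by hub and the arm-by-hub interaction for both primary outcomes, to show whether one delivery drives the result.
3. State that the pooled effect and its confidence interval are conditional on these three hub deliveries. The fixed effect does not widen the interval for wider inference, and three hubs are too few to estimate a delivery variance.

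**Cost.** No change to randomisation or delivery is needed; hub follows from centre location. The models lose two degrees of freedom, or four with the interaction. Hub-specific estimates will be imprecise: with a third of the centres each, the SE is about √3 × 0.0607 = 0.105 to √3 × 0.0714 = 0.124, so 95% intervals of roughly ±0.21 to ±0.24 SD. The claim also becomes more modest. If the SAP already contains these terms, only the statement of scope remains to be added.
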